##### Thirty‐six‐item short form health survey

The 36‐item short form health survey (SF‐36) is a tool frequently used for measurement of health‐related quality of life (Ware, 2000), validated and reliable in measuring self‐reported general health in individuals with chronic NP (de Vries et al., 2015). It comprises of 36 items, covering eight different domains of health: physical functioning; bodily pain; role limitations owing to physical health problems; role limitations owing to personal or emotional problems; emotional well‐being; social functioning; energy/fatigue; and general health perceptions. For the purpose of this study, the score from all domains will be averaged to provide a single SF‐36 score, with a higher score indicating a more favourable health state.

#### Physical outcome measurements

2.6.2

Figure 3 depicts the flowchart of assessment conducted at each data collection session.

**FIGURE 3 eph13343-fig-0003:**
[figure not shown]
Assessment flowchart at each data collection session. Abbreviations: CPM, conditioned pain modulation assessment; CPT, cold pain threshold; EIH, exercise‐induce hypoalgesia assessment; [La], blood lactate concentration assessment; PPT, pain pressure threshold; TS, temporal summation assessment.

##### Primary outcome measures

###### Exercise‐induced hypoalgesia

Exercise‐induced hypoalgesia will be assessed through pain pressure threshold (PPT) measurement, followed by a fatigue‐inducing exercise stimulus, and lastly, the same PPT measurements. The PPT will be measured using Echo Wireless Algometer (JTECH Medical, UT, USA). The PPT will be measured at two sites; (1) over the C5/C6 spinous process in the cervical spine; and (2) over the muscle belly of the left tibialis anterior. To ensure accurate measurement, an ‘x’ will be marked on the testing site with a marker during baseline assessment, and the same site will be used for postexercise PPT assessment. Pressure will be applied on the testing site at a rate of ∼5 N/s. Participants will be asked to state verbally when the sensation changes from ‘comfortable’ pressure to ‘unpleasant’ pain sensation. Triplicate reading, with a 30 s interstimulus interval, will be taken at each site, and the mean values will be used for analysis. The PPT measurements will be taken before and after the fatigue‐inducing exercise stimulus. The fatigue‐inducing exercise stimulus will be an isometric wall‐squat. Participants will be asked to maintain a wall‐squat position until fatigue or for a maximum of 3 min.

###### Temporal summation

Temporal summation (TS) will be induced using a 256 mN punctate needle stimulator or ‘PinPrick’ (MRC Systems, Heidelberg, Germany) as the noxious stimuli, at two sites: (1) over the C5/C6 spinous process in the cervical spine; and (2) dorsal surface of the dominant hand between the second and third metacarpals. An ‘x’ will be marked at the testing site to ensure accuracy for baseline and postexercise assessment. In the test, a single stimulus will be applied initially, and participants will be instructed to rate the pain intensity verbally. Then after a period of 10 s, a series of 10 identical punctate stimuli will be applied at a frequency of 1 Hz, which has been shown to be sufficient to induce TS. The participant will state verbally the pain rating immediately following the last stimulus. A printed NPRS, labelled with digits from 0 to 10, with ‘0’ indicating ‘no pain’ and ‘10’ being ‘extremely painful’, will be displayed in front of the participant.

###### Conditioned pain modulation

Conditioned pain modulation (CPM) will be measured using the PPT as the test stimulus and the cold pressor test as the conditioning stimulus. The PPT will be measured using Echo Wireless Algometer (JTECH Medical, UT, USA). The baseline PPT (PPTbase) is obtained from EIH assessment. The participants will be instructed to immerse their non‐dominant hand in an ice‐bath (up to the wrist) and will be motivated through verbal encouragement to maintain immersion for the duration of the defined period of 120 s. Participants will be instructed to state verbally when he/she begins to feel pain. The cold pain threshold is the time (in seconds) between the immersion and the verbal confirmation of pain sensation. The cold pressor pain tolerance is the total time (in seconds) of immersion. A single PPT will be measured over the previously marked site on the tibialis anterior at 30, 60 and 90 s and at the time of cold pain threshold occurring during immersion.

##### Secondary outcome measures

###### Lactate concentration

The [La] will be analysed using the Lactate Scout 4 lactate analyser (SensLab, Leipzig, Germany). A drop of blood, obtained using a single‐use lancing device on the fingertip, will be required for analysis. To ensure accuracy in measurement, the manufacturer's protocol guidelines will be followed.

### Exercise interventions

2.7

All assessment sessions will be conducted at The University of Adelaide.

#### HIGH intervention

2.7.1

Participants will put on the Polar HR monitor chest strap (Polar H10; Polar Electro Oy, Kempele, Finland). The HR monitor will be connected to a bluetooth‐enabled device, which will display the HR. After measuring the resting HR and blood pressure, [La] will be measured. The rating of perceived exertion (RPE) scale will be explained to the participants. The RPE will be determined using Borg 6–20 point‐category scale (Williams, 2017). The participant's 75% of age‐predicted maximum HR [i.e., 0.75 × (220 − age in years)] will be calculated; this will be used as the target HR during exercise.

Participants will then go onto the stationary bicycle, with the seat height adjusted for optimal cycling posture. Participants will use the same bicycle, with the same adjustment made, on both sessions. After a quick instruction briefing to ensure safety, participants will then complete a standardized, submaximal bicycle aerobic exercise protocol, based on the aerobic power index (API) protocol. The API protocol has been found to be a safe and reliable submaximal exercise test for individuals with various clinical conditions (Furzer et al., 2012; Wallman et al., 2003), including chronic NP (Ickmans et al., 2017; Smith et al., 2017, 2020). The participants will start to cycle at 60–70 rpm at level 1 resistance, and the resistance will be increased by one or two levels every minute until attainment of the target HR. The increment of resistance level will be controlled by the researcher and will be based on the participant's HR response. The participants will then continue to cycle at this power output for 30 min. Heart rate and RPE will be recorded each minute during the increase in power output, then once every 3 min until the end of the exercise session.

#### LOW intervention

2.7.2

The LOW intervention will follow the same procedure as HIGH, except for the intensity of the exercise. The participant's target HR will be 50% of age‐predicted maximum HR.

### Sample size

2.8

For this clinical trial, the sample size is calculated based on PPT. Calculations for an appropriate sample size were performed with G*Power (v.3.1.9.6; Dusseldorf, Germany) (Faul et al., 2007). Given that there are no data on aerobic exercise testing with similar intervention groupings in chronic NP, the a priori power analysis was conducted based on data from an exercise intervention study with similar intervention grouping (Taimela et al., 2000). The sample size of this study is calculated based on the difference in mean PPTs (25.0 ± 19.7; 42.1 ± 27.2) between two different exercise interventions, a desired two‐tailed α = 0.05, β = 0.20, and an allocation ratio of 1:1. The calculations revealed that 64 participants would be sufficient. However, to allow a loss to follow‐up of 20% and taking a conservative approach, a total of 80 participants with chronic NP will be recruited.

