**FIGURE 1 eph13343-fig-0001:**
[figure not shown]
Schedule of enrolment, interventions and assessments. Abbreviations: CPM, conditioned pain modulation; EIH, exercise‐induced hypoalgesia; GPAQ, global physical activity questionnaire; NDI, neck disability index; PCS, pain catastrophizing scale; SF‐36, 36‐item short form survey; ‐t_1_, enrolment week 0; t_0_, allocation; t_1–2_, intervention, baseline and post‐intervention assessments; TS, temporal summation; TSK, Tampa scale of kinesiophobia.

This study is a randomized crossover trial, in which all participants will take part in all interventions, but the order in which they are assigned to the interventions is randomized. Participants will attend the first data collection session, during which baseline questionnaires and physical assessments will be measured, followed by the intervention, and a post‐intervention physical assessment will be measured. There will be a 1‐ to 2‐week washout period before the second data collection session, which is identical to the first session minus the baseline questionnaires, with a different intensity of intervention.

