### Statistical analysis

2.9

All data will be analysed via scatterplots, boxplots and Kolmogorov–Smirnov statistics to evaluate normality. Normally distributed data will be reported as the means and 95% confidence interval. Other data will be reported as the median and interquartile range. Parametric tests will be used for normally distributed data, and non‐parametric tests for non‐normal distributed data, to analyse between‐group differences for physical outcome measures and baseline questionnaires and physical measures.

To test for carryover effects, the sum of the measured values in the sessions for each patient will be calculated and compared across the two groups with Student's unpaired *t*‐test (Wellek & Blettner, 2012). A *P*‐value of >0.05 indicates no carryover effects, and the ‘washout’ duration is sufficient. To determine the statistical difference between HIGH and LOW, the within‐subject difference in outcome parameters between both sessions will be calculated using Student's unpaired *t*‐test. If there is a statistical significance, a regression model will be conducted to evaluate the effect of exercise intensity (HIGH vs. LOW) on CS measures. The fixed effect of time (baseline and postexercise), exercise intensity and study group will be included in the model, with age as a covariate. If no statistical difference is detected, repeated‐measures ANOVA will be performed to assess significant differences between both groups; the within‐subject factor will be defined as ‘time’, with ‘group’ as a between‐subject factor. The significance level will be adjusted by the number of comparisons using Bonferroni correction.

Multivariate regression analysis will be used to analyse the association between [La] and EIH. In order to examine the relationship between individual measures of CS (EIH, CPM and TS), separate regressions will be conducted. Models will be adjusted for age, sex, education level, physical activity level, NDI, PCS and TSK. Statistical significance is set at *P* < 0.05.

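### The sample size of 64 comes from an independent two-group calculation at unadjusted alpha, so the stated 80% power does not describe this crossover; on the plan's inputs the error is conservative unless the within-person correlation is negative

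*Protocol article*

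**What the plan says.** Section 2.8 (Sample size) says that "the sample size is calculated based on PPT". It uses the "difference in mean PPTs (25.0 ± 19.7; 42.1 ± 27.2) between two different exercise interventions", taken from another exercise study, with two-tailed "α = 0.05, β = 0.20, and an allocation ratio of 1:1". It concludes: "The calculations revealed that 64 participants would be sufficient". After an allowance of 20% for loss to follow-up, "a total of 80 participants with chronic NP will be recruited". The section gives no within-person correlation, no SD of a within-person difference and no multiplicity adjustment.

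Section 2.2 (Setting and design) describes a randomized crossover in which "all participants will take part in all interventions". Section 2.4 (Procedures) sets the two sequences as HIGH–LOW and LOW–HIGH, so the 1:1 randomization is to order, not to intensity.

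Section 2.9 (Statistical analysis) compares HIGH with LOW on the within-subject difference between sessions, by an unpaired t-test. It closes the account of the HIGH–LOW and ANOVA analyses with: "The significance level will be adjusted by the number of comparisons using Bonferroni correction". Neither the number of comparisons nor the tests covered are given.

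**The concern.** The calculation and the design do not match in two respects.

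- **Model.** The calculation treats the two intensities as separate groups of people. In the trial, 64 completers supply 64 values at each intensity, not 32, and the relevant variability is the SD of the within-person HIGH–LOW difference.
- **Alpha.** The calculation spends the full 0.05 on one comparison. Section 2.6.2 (Physical outcome measurements) lists three primary outcomes (EIH, TS and CPM), the first two at two sites each, and section 2.9 foresees a correction.

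What is at stake is interpretation, not recruitment. The power statement belongs to a different test from the one planned, so a reader cannot tell from it how sensitive the trial is. The article's Discussion presents the sample size as a major strength, so its basis should fit the design.

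**Working it through.** **Inputs from section 2.8:** means 25.0 and 42.1, SDs 19.7 and 27.2, two-sided alpha 0.05, power 0.80, 1:1 allocation, loss 20%.

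**Assumed, because the article does not give them:** the within-person correlation rho (0, 0.5 and 0.7, with −0.5 as a stress case) and the number of comparisons k (1, 3 and 5).

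**Step 1: reproduce the plan's figure.**
- Difference = 42.1 − 25.0 = 17.1.
- Pooled SD = √((19.7² + 27.2²)/2) = 23.75.
- d = 17.1/23.75 = 0.720.
- Unpaired t-test, noncentral t: power is 79.7% with 31 per group and 80.9% with 32 per group, so the total is 2 × 32 = 64.
- 64/(1 − 0.20) = 80.

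Both stated figures reproduce. A paired t-test on the same means and SDs does not return 64: it gives 33 at rho 0 and 18 at rho 0.5.

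**Step 2: the same inputs in the planned crossover test.** With two equal sequence groups and an unpaired t-test on the session differences:
- SD of the within-person difference = √(19.7² + 27.2² − 2 × rho × 19.7 × 27.2)
- noncentrality = (17.1/SD of difference) × √N, with N − 2 degrees of freedom

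| rho | SD of difference | Completers for 80% power, alpha 0.05 |
|---|---|---|
| −0.5 | 40.8 | 48 |
| 0 | 33.6 | 34 |
| 0.5 | 24.3 | 20 |
| 0.7 | 19.4 | 14 |

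**Step 3: power for 17.1 with 64 completers (62 degrees of freedom).**

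| rho | alpha 0.05 | 0.05/3 | 0.05/5 |
|---|---|---|---|
| −0.5 | 91% | 81% | 75% |
| 0 | 98.0% | 94.3% | 91.7% |
| 0.5 | >99.9% | 99.9% | 99.8% |

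**Step 4: difference detectable with 80% power and 64 completers.**

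| rho | alpha 0.05 | 0.05/5 |
|---|---|---|
| 0 | 12.0 | 14.7 |
| 0.5 | 8.7 | 10.7 |
| 0.7 | 6.9 | 8.5 |

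Ignoring the pairing makes the required number too large; ignoring Bonferroni makes it too small. For rho of 0 or more, the first effect outweighs the second at every k shown.

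**The case against.** The best defence is that nothing is miscalculated and nothing unsafe follows. The inputs do return 64, and 64 does become 80. On the plan's own means and SDs, 64 completers are sufficient for 17.1 whenever rho is not negative, so the quoted conclusion is not shown to be false. That stands: the fault is a mismatch between model and design, not an arithmetic slip.

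Three further points stand.

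- The Bonferroni sentence directly follows the fallback ANOVA and does not say which tests it covers, and section 2.9 also sets significance at P < 0.05. The adjusted alpha is therefore unknown, and the divisors 3 and 5 are only illustrations.
- The SDs come from another study. EIH here is a change in PPT around a wall-squat, measured before and after cycling, so nothing shows that 19.7 and 27.2 apply to the contrast analysed.
- Section 2.8 plans on 17.1 but does not call it the smallest detectable difference, and a null result would be read mainly from its confidence interval.

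It might also be said that an independent-groups model was chosen for caution. The article does not say so: its remark about a conservative approach accompanies the step from 64 to 80.

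A reader might infer from the omitted Bonferroni correction that the trial is underpowered. The document does not support that. Power falls clearly below 80% if the correction is applied to the two-group model, but that model is not this trial.

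**Conclusion.** The point holds as a mismatch between the calculation and the design. The 80% power stated for a difference of 17.1 belongs to two independent groups of 32 at unadjusted 0.05, not to the crossover test in section 2.9.

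The net error is conservative for non-negative rho. At rho 0, power with 64 completers is about 98% unadjusted and 94% at 0.05/3, and positive rho raises both. Among the cases computed here, power drops below 80% only with negative correlation combined with heavier correction (75% at rho −0.5 and 0.05/5).

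These figures rest on the borrowed means and SDs, an assumed rho and an assumed k. They show the direction and rough size of the discrepancy and should not be adopted as the trial's true power. The planned number does not need to change.

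**What to change.** Keep N = 80 and rewrite section 2.8 for the crossover contrast. The new text should state:

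1. the assumed SD of the within-person HIGH–LOW difference, or rho with a range, on the scale of the outcome actually analysed;
2. which tests the Bonferroni correction covers, the number of comparisons and the resulting alpha;
3. the power and the detectable difference with 64 completers under those assumptions;
4. that 64 came from an independent-groups calculation and is conservative if rho is not negative.

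Give power as a range over the assumptions and not as one headline figure, since rho, the SDs on the analysed scale and the number of comparisons are all uncertain. The cost is one rewritten paragraph, plus a stated number of comparisons in section 2.9. Recruitment and the planned tests stay as they are.

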### Statistical analysis

2.9

All data will be analysed via scatterplots, boxplots and Kolmogorov–Smirnov statistics to evaluate normality. Normally distributed data will be reported as the means and 95% confidence interval. Other data will be reported as the median and interquartile range. Parametric tests will be used for normally distributed data, and non‐parametric tests for non‐normal distributed data, to analyse between‐group differences for physical outcome measures and baseline questionnaires and physical measures.

To test for carryover effects, the sum of the measured values in the sessions for each patient will be calculated and compared across the two groups with Student's unpaired *t*‐test (Wellek & Blettner, 2012). A *P*‐value of >0.05 indicates no carryover effects, and the ‘washout’ duration is sufficient. To determine the statistical difference between HIGH and LOW, the within‐subject difference in outcome parameters between both sessions will be calculated using Student's unpaired *t*‐test. If there is a statistical significance, a regression model will be conducted to evaluate the effect of exercise intensity (HIGH vs. LOW) on CS measures. The fixed effect of time (baseline and postexercise), exercise intensity and study group will be included in the model, with age as a covariate. If no statistical difference is detected, repeated‐measures ANOVA will be performed to assess significant differences between both groups; the within‐subject factor will be defined as ‘time’, with ‘group’ as a between‐subject factor. The significance level will be adjusted by the number of comparisons using Bonferroni correction.

Multivariate regression analysis will be used to analyse the association between [La] and EIH. In order to examine the relationship between individual measures of CS (EIH, CPM and TS), separate regressions will be conducted. Models will be adjusted for age, sex, education level, physical activity level, NDI, PCS and TSK. Statistical significance is set at *P* < 0.05.

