### Procedures

2.4

Participants who meet the inclusion criteria will be invited to attend two testing sessions: one to perform high‐intensity submaximal aerobic bicycle exercise (HIGH); and a second to complete a low‐intensity submaximal aerobic bicycle exercise (LOW). The order of these two testing sessions will be randomized. Participants will be asked to refrain from analgesics on the day of testing and to abstain from physically demanding activities, including exercise, for 48 h before testing. Participants will also be asked to abstain from nicotine, alcohol and caffeine for 12 h before testing.

Participants will be given a detailed explanation about the research study and the requirements of them. Informed consent will be obtained from the participants before collecting any data. Figure 2 depicts the flowchart of study procedure and the assessments conducted at each assessment time point. Participants will be randomized into two main groups, termed the INV‐A group and the INV‐B group, with INV‐A doing HIGH–LOW and INV‐B doing LOW–HIGH. Participants will wait 10 min before commencing the exercise intervention to prevent a carryover effect from the baseline physical assessments influencing exercise. During the waiting time, resting heart rate (HR) and blood pressure will be measured, and appropriate warnings and precautions will be briefed. Participants will then complete the assigned exercise intervention, immediately followed by postexercise assessment. The order of testing will be kept constant within each testing session, both before and after exercise. To prevent a carryover effect, the sessions will be scheduled 1–2 weeks apart.

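### The model that estimates HIGH versus LOW runs only after a significant t-test; the other branch has no intensity term, and no interval for the contrast is promised

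*Protocol article*

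**What the plan says.** All of the analysis text is in the protocol article, section 2.9 (Statistical analysis).

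- **Summaries.** "Normally distributed data will be reported as the means and 95% confidence interval". For the rest, "Other data will be reported as the median and interquartile range". No other interval is named, and the sentence does not say which quantity it covers.
- **HIGH-LOW test.** For each participant "the within‐subject difference in outcome parameters between both sessions will be calculated", and an unpaired t-test is applied. No condition is attached to this step.
- **If significant.** "If there is a statistical significance, a regression model will be conducted to evaluate the effect of exercise intensity (HIGH vs. LOW) on CS measures". This model contains time, intensity and study group, with age as covariate. The sentence directly follows the HIGH-LOW t-test, and I read the condition as referring to that test.
- **If not significant.** A repeated-measures ANOVA "will be performed to assess significant differences between both groups", with time as the within-subject factor and group as the between-subject factor.

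Section 2.4 (Procedures) defines the groups as sequences, "with INV‐A doing HIGH–LOW and INV‐B doing LOW–HIGH". Section 2.2 (Setting and design) says that every participant takes part in both interventions.

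**The concern.** The primary aim is the immediate effect of exercise on central sensitization, studied by comparing two intensities within person. The HIGH-LOW difference and its precision are therefore the main result, whether the test is positive or null. The plan makes the form of analysis depend on the p-value, and only the significant branch contains intensity. An outcome that misses significance goes to a model that compares people by the order in which they did the sessions. A reader could then not tell evidence of little difference from data too imprecise to say.

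The interval sentence does not fill the gap. If it is applied to the HIGH and LOW sessions separately, the intervals reflect spread between people, which the crossover comparison largely removes. They would not show the precision of the within-person contrast.

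Finally, if estimates are presented only for outcomes that pass the test, those presented will on average be too large. How much depends on the true effect and the correlation.

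**Working it through.** **Inputs.** Section 2.8 (Sample size) gives PPT 25.0 (SD 19.7) and 42.1 (SD 27.2), two-sided alpha 0.05, power 0.80, 1:1 allocation, 64 participants before loss, 20% loss and 80 recruited. The within-person correlation (rho) between sessions is not given, so I show a range. The SDs are taken to apply to the value analysed in each session.

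**1. The plan's own figure.** The difference is 42.1 - 25.0 = 17.1. The pooled SD is sqrt((19.7² + 27.2²)/2) = 23.75, so d = 0.72. A two-independent-sample t-test needs 32 per group, 64 in total (power 0.809), and 64/0.80 = 80. The stated sizes reproduce.

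**2. Does the non-significant branch contain intensity?** Its factors are time and group. Group is INV-A or INV-B, and each group does both HIGH and LOW. No term in the ANOVA separates HIGH from LOW, so it yields no estimate of that contrast.

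**3. Interval for the contrast, if it were reported.** Take session 1 minus session 2 for each person. The mean of this in the HIGH-LOW sequence minus the mean in the LOW-HIGH sequence equals twice the HIGH-minus-LOW effect. Half of it is the estimate. With 32 per sequence, its variance is (1/4)(SD_d²/32 + SD_d²/32) = SD_d²/64, so SE = SD_d/8.

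SD_d = sqrt(19.7² + 27.2² - 2·rho·19.7·27.2), and the half-width is t(62)·SD_d/8, with t(62) = 2.00.

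| rho (assumed) | SD_d | 95% half-width |
|---|---|---|
| 0 | 33.6 | 8.4 |
| 0.5 | 24.3 | 6.1 |
| 0.7 | 19.4 | 4.9 |
| 0.9 | 12.8 | 3.2 |

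Intervals around the two separate session means have half-widths of 4.9 and 6.8 at every rho, so they carry no information about the precision of the contrast. Combining the sessions as if independent gives about 8.4 at any rho, which is 8.4/6.1 = 1.4 to 8.4/3.2 = 2.6 times the correct half-width for rho 0.5 to 0.9. At rho 0 there is no difference.

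An estimate near zero with half-width 6.1 has an upper limit near 6, well below 17.1. More generally, a non-significant estimate lies within one half-width of zero, so its upper limit is below two half-widths: 12.2, 9.8 or 6.4 at rho 0.5, 0.7 or 0.9.

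**4. Inflation from keeping only significant estimates.** Let lambda = true effect/SE. The ratio of the expected absolute estimate, given p < 0.05, to the true effect is E(|z| given |z| > 1.96)/lambda. Example at half the planned effect and rho 0.5: lambda = 8.55/3.04 = 2.81 and power = 0.80. With the opposite tail negligible, the excess is phi(0.85)/(2.81 × 0.803) = 0.278/2.256 = 0.12.

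| True effect | rho | Power | Inflation |
|---|---|---|---|
| 17.1 (planned) | 0 | 0.98 | 1.1% |
| 17.1 | 0.5 | about 1.00 | about 0% |
| 8.55 (half) | 0 | 0.53 | 37% |
| 8.55 | 0.5 | 0.80 | 12% |
| 8.55 | 0.7 | 0.94 | 4% |
| 4.28 (quarter) | 0 | 0.18 | 145% |
| 4.28 | 0.5 | 0.29 | 84% |
| 4.28 | 0.7 | 0.42 | 53% |

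Simulating the two-sequence t-test agrees: at rho 0.7 and a quarter of the effect, power was 0.41 and the ratio 1.53; at rho 0 and half the effect, 0.52 and 1.37.

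**The case against.** The strongest reply is that the within-subject difference is calculated for everyone before any gate, and the t-test on it can supply an estimate and an interval. On that view the condition governs only a follow-up regression, and a condensed article may leave the printing of the t-test's interval to the full plan. The formal test already uses within-subject differences, so nobody is asked to judge by overlapping intervals. The data are also to be deposited publicly (section 4, Data management), so the contrast could be recovered later.

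Much of this stands, and it rules out three stronger readings.

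- *That the stated intervals are intervals of session means.* The sentence is a general rule for normally distributed data and could cover the within-subject difference. Session means is one natural reading, not the text.
- *That a null result has no interval.* One can be obtained from the t-test step. It is simply not promised.
- *That a positive result is inflated.* At the planned effect the inflation is negligible. It comes from selecting significant results; the unselected estimate is not biased by it.

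The reply does not remove the gate. The conditional rule is stated, not left open, and the branch prescribed for non-significant outcomes leaves out intensity. The t-test's default interval is also not the HIGH-LOW interval: on session-1-minus-session-2 differences it covers twice the effect until halved.

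**Conclusion.** The point holds for the gate and for the missing commitment to the contrast. As written, whether HIGH versus LOW is modelled depends on a p-value, and a non-significant outcome goes to an ANOVA that cannot answer the primary question. No interval for the contrast is named.

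The loss is largest for null results. At the plan's SDs with 64 completers, the half-width of about 6.1, 4.9 or 3.2 (rho 0.5, 0.7 or 0.9) would let an estimate near zero exclude the planned 17.1. These figures rest on the borrowed planning SDs and an assumed correlation.

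The inflation concern is secondary. It is about 1% or less at the planned effect, and becomes material only at about half that effect or less with low to moderate correlation (12% at half the effect and rho 0.5), or at smaller effects generally. Section 2.8 takes 17.1 from another exercise study because no data with similar groupings existed in chronic neck pain, so a smaller true effect cannot be ruled out.

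The gate should be removed before analysis.

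**What to change.** Delete the significance condition and the alternative ANOVA branch as a route to the intensity question. For every primary outcome and site, report the HIGH-minus-LOW difference with its 95% CI whatever the p-value. Obtain it in one of two equivalent ways, fixed in advance:

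- half the difference between the sequence groups' mean session-1-minus-session-2 differences; or
- the intensity term of one pre-specified crossover model with intensity, period, sequence and participant.

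Base conclusions on that estimate and interval. State that the existing mean-and-CI rule is descriptive and is not the measure of precision for HIGH versus LOW.

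The cost is a few sentences of analysis wording and one table column. No new data are needed.

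### A non-significant test on summed sessions cannot show that there is no carryover or that the washout is long enough

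*Protocol article*

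**What the plan says.** Section 2.9 (Statistical analysis) sets out the carryover test: "the sum of the measured values in the sessions for each patient will be calculated and compared across the two groups", using an unpaired t-test. It then fixes how the result is read: a P-value above 0.05 "indicates no carryover effects, and the ‘washout’ duration is sufficient". The section gives no power, equivalence margin or confidence-interval criterion for this test, and no action if P is 0.05 or less. The next step described is the HIGH–LOW comparison.

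Section 2.8 (Sample size) bases the trial on "the difference in mean PPTs (25.0 ± 19.7; 42.1 ± 27.2) between two different exercise interventions", with "α = 0.05, β = 0.20, and an allocation ratio of 1:1". It concludes: "The calculations revealed that 64 participants would be sufficient". The recruitment target follows: "to allow a loss to follow‐up of 20% and taking a conservative approach, a total of 80 participants". Carryover plays no part in this calculation.

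Two other places bear on the washout. Sections 2.2 and 2.4 put the sessions 1 to 2 weeks apart. The Discussion says that exercise-induced hypoalgesia (EIH) after a single bout lasts up to 30 min.

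**The concern.** The rule reads failure to reject as evidence of absence. That would matter little if the test were powerful, but it is built on the least precise contrast in a two-period crossover. The within-person sum keeps whatever variation between people remains in the analysed value, whereas the HIGH–LOW comparison removes it. A higher correlation between sessions therefore sharpens the HIGH–LOW test and blunts the carryover test.

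Two things are at stake. The report could state that the washout was sufficient on evidence that cannot show it. And a differential carryover large enough to distort HIGH–LOW could pass unnoticed behind a reassuring P-value.

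**Working it through.** **Inputs from Section 2.8.** Means 25.0 and 42.1, SDs 19.7 and 27.2, two-sided alpha 0.05, power 80%, 1:1 allocation, 64 evaluable and 80 recruited. That is 32 per sequence after the allowed loss, or 40 with none.

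**Assumed.** The correlation ρ between a person's two session values is not in the document, so it is varied from 0 to 0.9. The planning SDs are taken to apply to the analysed value.

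**Step 1: the plan's own figure.** Difference = 42.1 − 25.0 = 17.1. Pooled SD = √((19.7² + 27.2²)/2) = √(1127.93/2) = 23.75, so d = 17.1/23.75 = 0.72. An exact two-sample t calculation gives 32 per group (64 in total, power 80.9%), and 64/0.8 = 80. Both stated figures reproduce.

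**Step 2: what the carryover test estimates.** Let λ be the carryover from HIGH minus the carryover from LOW.
- The sums differ between sequences by λ, apart from sampling error.
- The HIGH–LOW estimate, averaged over the two sequences, is shifted by λ/2 in absolute size.
- Carryover that is equal after HIGH and LOW appears in neither.

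**Step 3: precision of the sum.** SD(sum) = √(19.7² + 27.2² + 2ρ × 19.7 × 27.2) = √(1127.93 + 1071.68ρ). At ρ = 0.5 this is √1663.77 = 40.8. With 32 per sequence the standard error is 40.8 × √(2/32) = 10.2. The whole planned difference is then only 17.1/10.2 = 1.7 standard errors.

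**Step 4: probability of missing a carryover** (P above 0.05, noncentral t). Half the planned difference is 17.1/2 = 8.55.

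| Per sequence | ρ | SD(sum) | Missed, λ = 8.55 | Missed, λ = 17.1 | λ detected with 80% power |
|---|---|---|---|---|---|
| 32 | 0 | 33.6 | 83% | 48% | 23.9 |
| 32 | 0.3 | 38.1 | 86% | 58% | 27.1 |
| 32 | 0.5 | 40.8 | 87% | 62% | 29.0 |
| 32 | 0.7 | 43.3 | 88% | 66% | 30.8 |
| 32 | 0.9 | 45.7 | 89% | 69% | 32.5 |
| 40 | 0 | 33.6 | 80% | 39% | 21.3 |
| 40 | 0.3 | 38.1 | 83% | 49% | 24.1 |
| 40 | 0.5 | 40.8 | 85% | 54% | 25.9 |
| 40 | 0.7 | 43.3 | 86% | 59% | 27.5 |
| 40 | 0.9 | 45.7 | 87% | 62% | 29.0 |

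**Step 5: what this means for HIGH–LOW.** If the carryover enters the analysed value, λ = 8.55 shifts HIGH–LOW by about 4.3 and λ = 17.1 by about 8.6, half the planned effect. The λ detected with 80% power (21.3 to 32.5) corresponds to a bias of 10.7 to 16.3, which is 62% to 95% of 17.1. Under the same assumptions the HIGH–LOW test has at least 98% power for 17.1, so the check is far weaker than the comparison it is meant to protect.

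**The case against.** The strongest defence is that the washout rests on design, not on this test. One week is 7 × 24 × 2 = 336 half-hours, against a stated EIH duration of up to 30 min, and Section 2.4 also asks for 48 h without demanding activity before testing. Material carryover is therefore unlikely. This stands and lowers the practical impact. It does not rescue the rule, because the text draws its conclusion about the washout from the P-value and not from the design.

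Second, the size of the problem depends on assumptions. At low correlation the test does not miss most carryovers as large as the planned effect: it detects 52% at ρ = 0 with 32 per sequence, and 51–61% at ρ of 0.3 or less with 40. Low correlation is possible if the analysed values are differences, as EIH, temporal summation and conditioned pain modulation may be. This also stands, which is why the range is shown. For carryover of half the planned effect, most are missed at every correlation tried.

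Third, Section 2.6 has the central pain measures taken before and after exercise in each session. If change scores are analysed, a level shift common to the session-2 baseline and postexercise values cancels and does not bias HIGH–LOW. Section 2.9 does not say whether the summed values are raw or change scores, so the bias is conditional.

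A reader might go further in two ways that the document does not support:
- That the test decides which analysis is run. No branch is tied to it. The later condition on statistical significance follows the HIGH–LOW test and most naturally refers to that.
- That repeating the test over several outcomes makes a false carryover signal likely. Section 2.9 does not say how many such tests there will be, the measures are related, and it mentions a Bonferroni adjustment whose reach is not spelled out. No false-alarm rate can be derived from this.

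**Conclusion.** The rule is wrong as written. P above 0.05 on this test cannot support a finding of no carryover or of a sufficient washout. With the planning SDs, 32–40 per sequence and an assumed correlation of 0–0.9, the test misses 80–89% of carryovers of half the planned difference and 39–69% of those equal to the whole. The latter figure is 62–69% with 32 per sequence and a correlation of 0.5–0.9. Other outcomes may have different variances.

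The fault lies in interpretation. It does not show that carryover exists or that the HIGH–LOW result will be biased. The protocol's own timing makes material carryover unlikely, so the practical impact is modest.

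**What to change.** In Section 2.9:
- Delete the sentence that reads P above 0.05 as no carryover and a sufficient washout.
- Justify the washout by design: 1–2 weeks between sessions against the protocol's stated EIH duration of up to 30 min.
- Report the carryover contrast as an estimate with a 95% confidence interval, and infer nothing about absence from non-significance.
- State that the HIGH–LOW analysis uses both sessions whatever this contrast shows. The text already implies this; saying so removes doubt.
- Add a supplementary check: the session-2 minus session-1 difference in pre-exercise baseline, compared between sequences and also reported with a confidence interval. It does not detect a carryover that alters only the response to the session-2 exercise, so it adds to the sum contrast and does not replace it.

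The cost is a few sentences. Both baselines are already measured (Sections 2.2 and 2.6), so no new data, visits or participants are needed.
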